#### Secondary Outcomes

The secondary outcome is the cost-effectiveness of AI-assisted screening compared with conventional screening, assessed using the incremental cost-effectiveness ratio, under the societal perspective. Cost-effectiveness analyses will incorporate both the direct and indirect medical costs related to screening, diagnostic evaluation, and treatment.

#### Exploratory Outcomes

Exploratory outcomes include (1) screening participation rate, assessed by the number of participants and nonparticipants; (2) referral completion rate, defined as the proportion of referred participants who completed ophthalmologic confirmatory evaluation within the prespecified 2-month follow-up period; (3) patient satisfaction, evaluated using a posttrial survey; (4) whether AI-assisted screening reduces clinical decision-making time and physician workload, evaluated using a posttrial survey; (5) time to diagnosis of DR or AMD; and (6) visual loss as the long-term outcome.

### Sample Size Estimation

The estimated prevalence of any DR (across stages 1-4) and AMD is 27% and 10%, respectively [29,30]. For this study, the sample size is calculated based on the assumption that 10% of patients with diabetes aged ≥20 years are diagnosed with clinically significant DR (stages 2 to 4) in the Department of Family Medicine and the Department of Geriatrics and Gerontology. Using AI-assisted diagnostic tools, the detection is assumed to increase to 15% [31].

In this real-world pragmatic setting, there was no prior evidence on the referral rates for eye disease screening in Taiwan. This study therefore assumed a referral rate of approximately 70% based on large-scale pragmatic screening trials of fecal occult blood testing and *Helicobacter pylori* stool antigen testing in Taiwan [20,21]. Accordingly, it is assumed that 70% of screen-positive individuals will be successfully referred to ophthalmologists for further examination and with a 2-tailed test, a type I error (α) of .05, and a type II error (β) of .10, the required sample size is 2612 participants (1306 per group). Approximately 870 participants are expected to be enrolled annually over an anticipated 3-year study period.

For patients aged ≥50 years in the Department of Family Medicine and the Department of Geriatrics and Gerontology in the NTUH, the prevalence of AMD is 5%, which is assumed to increase to 10% with the use of AI-assisted diagnostic tools. Assuming that 70% of the screening cases can be successfully referred to ophthalmologists and with a 2-tailed test, a type I error (α) of .05, and a type II error (β) of .10, the required sample size is 1650 participants (825 per group). Approximately 550 participants are expected to be enrolled per year.

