**Results:**

The study was funded in September 2024, began on October 2, 2025, and is expected to be completed in December 2027. After the pilot implementation phase without randomization, participants will be randomized 1:1 into two groups: (1) AI-assisted screening, and (2) usual physician-only screening. The primary outcomes will include the detection rates (defined as participants with confirmed DR or AMD among all screened participants) and the positive predictive values (defined as participants with confirmed DR or AMD among those who tested positive). Cost-effectiveness analyses will be performed using data derived from the trial results.

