## Methods

### Study Design

This study adopts a 2-phase design. The first phase is a pilot feasibility study conducted to evaluate system integration, workflow functionality, and operational readiness of AI-assisted retinal screening within routine clinical practice. The pilot phase began on October 2, 2025, and is expected to last for approximately 6 months to 1 year.

The decision to proceed to the second phase will be guided by referral rate–based criteria, based on pragmatic randomized trials [20,21], and progression to the second phase is not guaranteed.

The second phase is a multicenter, 2-arm, parallel-group, open-label pragmatic randomized clinical trial designed to evaluate the effectiveness of AI-assisted retinal screening compared with conventional physician-based screening. Owing to the nature of the intervention, blinding of the physicians performing the screening assessments is not possible. In addition, the ophthalmologists conducting the confirmatory diagnostic evaluations will not be blinded to group allocation, as the presence or absence of an AI-generated report may allow them to infer the assigned screening strategy. It reflects the real-world practice of using this AI instrument. Cost-effectiveness analyses will be conducted using trial data to simulate long-term economic benefits. The flowchart of this study is shown in Figure 1. The study followed the SPIRIT (Standard Protocol Items: Recommendations for Interventional Trials; Checklist 1) for RCT guideline [22].

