In addition, regarding the incomplete referral follow-up and missing confirmatory diagnoses in the pragmatic setting, the number and proportion of participants with missing outcome data will be summarized by study group, together with the reasons for missingness whenever available. The primary detection rate analysis will follow the intention-to-screen principle, in which screen-positive participants with missing confirmatory diagnosis will remain in the denominator but will not contribute to the numerator. For PPV analyses, participants with missing confirmatory diagnosis will be excluded from both the numerator and denominator. Post hoc mixed-effects regression analyses will be performed for these 2 outcomes accounting for other covariates as mentioned earlier.

A 2-sided *P* value of <.05 will be considered statistically significant. All statistical analyses will be conducted using the SAS software (version 9.4; SAS Institute).

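### The stated sample sizes need three years of enrolment, but the stated dates leave about 13 to 19 months for randomisation, so the 90% power is not reachable on that timetable

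*Protocol article*

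**What the plan says.** Sample Size Estimation sizes each disease separately, "with a 2-tailed test, a type I error (α) of .05, and a type II error (β) of .10". For DR it assumes that "10% of patients with diabetes aged ≥20 years are diagnosed with clinically significant DR (stages 2 to 4") and that detection rises to 15% with AI. For AMD it assumes 5% rising to 10%. It takes 70% of screen-positives to be successfully referred, and says there was no earlier evidence on referral for eye screening in Taiwan. The results are "the required sample size is 2612 participants (1306 per group") for DR and "the required sample size is 1650 participants (825 per group") for AMD.

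On pace, the same section says for DR: "Approximately 870 participants are expected to be enrolled annually over an anticipated 3-year study period". For AMD it gives about 550 a year.

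On dates, the Abstract (Results) says that the study "began on October 2, 2025, and is expected to be completed in December 2027" and that randomisation follows a pilot phase without randomisation. Study Design says that the pilot, begun on the same October date, "is expected to last for approximately 6 months to 1 year". Referral After a Positive Test sets the outcome review at 8 weeks after screening.

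On the analysis of the detection rate, Statistical Analysis says that "screen-positive participants with missing confirmatory diagnosis will remain in the denominator but will not contribute to the numerator".

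**The concern.** Two parts of the sizing do not fit the rest of the protocol.

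The first is the calendar. Three years of enrolment cannot lie between October 2025 and December 2027, and the first 6 to 12 months of that interval are not randomised. A reader who takes both the dates and the sizes at face value cannot tell whether the trial will end late, recruit faster or stop short. If it stops short, the stated power is lost.

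The second is how the 70% enters. Both sizes equal an ordinary two-proportion size divided by 0.7, which is the usual allowance for participants who leave the analysis. In the detection-rate analysis nobody leaves: screen-positives without confirmation count as non-cases. The 70% therefore shrinks both rates and the difference between them.

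**Working it through.** **Inputs.** From Sample Size Estimation: two-sided α = 0.05 (z = 1.960), power 90% (z = 1.2816), 10% v 15% (DR), 5% v 10% (AMD), referral completion 0.70, and 870 and 550 participants a year. Allocation is 1:1 (Randomization). Dates are as above.

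**Formulas.** Let V = [p₁(1−p₁) + p₂(1−p₂)]/(p₂−p₁)². The size per arm is n = (1.960 + 1.2816)² × V = 10.507 × V. Power with m per arm is Φ(√(m/V) − 1.960).

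**1. Reproducing the stated sizes.**
- DR: V = (0.09 + 0.1275)/0.0025 = 87, n = 914.1, and 914.1/0.7 = 1305.9 (stated 1306).
- AMD: V = (0.0475 + 0.09)/0.0025 = 55, n = 577.9, and 577.9/0.7 = 825.6 (stated 825).

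**2. Time needed.** 2612/870 = 3.0 years and 1650/550 = 3.0 years, so the yearly figures are the targets spread over three full years of enrolment.

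**3. Time available.** Eight weeks before the end of December 2027 is early November 2027. From the end of the pilot to that date is about 19 months (6-month pilot, ending early April 2026) or about 13 months (12-month pilot, ending early October 2026). Three years of enrolment would overrun by 36 − 19 = 17 to 36 − 13 = 23 months.

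**4. Participants reached at the stated pace.**
- DR: 870 × 13/12 = 942 to 870 × 19/12 = 1378.
- AMD: 550 × 13/12 = 596 to 550 × 19/12 = 871.
- Counting all 27 months from October 2025, pilot included, gives only 870 × 27/12 = 1958 and 550 × 27/12 = 1238.

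**5. Power if enrolment stops there.** With 70% completion and non-completers as non-cases, the rates are 7.0% v 10.5% (V = 129.9) and 3.5% v 7.0% (V = 80.7).

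| | Per arm | Power, rates × 0.7 | Power, rates already net of referral loss |
|---|---|---|---|
| DR, 13 months | 471 | 48% | 64% |
| DR, 19 months | 689 | 63% | 80% |
| AMD, 13 months | 298 | 48% | 64% |
| AMD, 19 months | 435 | 64% | 80% |

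**6. Power at the full stated sizes.**
- Rates × 0.7: DR Φ(√(1306/129.9) − 1.960) = 88.7%; AMD Φ(√(825/80.7) − 1.960) = 89.2%. Simulating the pooled two-proportion test gives 88.9% and 89.8%.
- Exact 90% on these rates needs 10.507 × 129.9 = 1365 per arm (DR) and 10.507 × 80.7 = 849 (AMD), that is 59 and 24 more per arm.
- Without any inflation (914 and 578 per arm), power on these rates would be 75.6% and 76.3%, so dividing by 0.7 recovers nearly all of the loss.
- At 60% completion (6% v 9%; 3% v 6%), power at the stated sizes is 83.0% and 83.8%.
- If the assumed rates are already net of referral loss, it is about 97% for both.

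**The case against.** **On the calendar.** The yearly figures are the targets divided by three, not stated ceilings, and nothing says that enrolment stops in December 2027 whether or not the target is met. The sites could recruit faster or the end date could move. This stands as a limit on the power figures, which hold only at the stated pace with a stop at the stated date. It does not remove the conflict. Meeting the DR target in 13 to 19 months needs about 2612 × 12/19 = 1650 to 2612 × 12/13 = 2411 a year, against 870 stated. The three-year study period might also be counted from the September 2024 funding, but no participant was enrolled before October 2025.

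**On the 0.7.** A reader might infer that dividing by 0.7 leaves the trial materially underpowered. The figures do not support that. With small rates, multiplying both by r raises the required size by roughly 1/r, so the division is nearly right even for the planned analysis. The gap of about one point is smaller than the uncertainty in a completion rate given as approximately 70%. The section also does not say how the 70% enters, or whether the assumed rates are before or after referral loss. On the second reading there is no shortfall at the stated sizes, though the 70% adjustment then has no purpose.

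**On lower completion.** The lack of evidence for 70% is openly stated, and Study Design already makes progression depend on referral-rate criteria from the pilot. The 60% scenario is therefore a sensitivity figure, not an error.

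**Conclusion.** The calendar conflict holds and is the material part. The sizes of 2612 and 1650, the pace of 870 and 550 a year, the pilot of 6 to 12 months and the December 2027 completion cannot all be true. At the stated pace and end date the trial reaches about 36 to 53% of either target (942/2612 to 1378/2612; 596/1650 to 871/1650). Power is then about 48 to 64%, or about 64 to 80% if the rates are net of referral loss. This assumes steady accrual from the end of the pilot and the last enrolment 8 weeks before the end of December 2027. It is not a forecast that the trial will end with that power, because the documents fix no such stop.

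The 0.7 issue is minor. It is a close but inexact correction that leaves about 88.7% and 89.2% at the stated sizes if the rates are before referral loss. The section should say which rates it means.

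**What to change.** 1. Reconcile the accrual period with the completion date: extend the end date, document a faster pace and its basis, or state a smaller reachable size. Restate the size and power that follow.
2. State whether 10% v 15% and 5% v 10% are before or after referral loss. If before, derive power from the post-referral rates and report 88.7% and 89.2% at 1306 and 825 per arm (or use 1365 and 849 for 90%). If after, explain or remove the division by 0.7.
3. Before randomisation starts, update these figures with the referral completion observed in the pilot.

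Items 2 and 3 cost a few lines of text and a short calculation, and need no extra participants if power is restated. Item 1 is also a text change if reduced power is accepted. Keeping the full sizes at the stated pace means running about 17 to 23 months past December 2027.

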### Referral After a Positive Test

The examination will be repeated for images that are of insufficient quality for clinical interpretation. Across both groups, ophthalmology referral will be provided for participants with DR of stages 2 to 4 or AMD of stages 3 to 4, whereas participants not meeting these severity thresholds will be advised to undergo regular annual follow-up examinations. Confirmatory diagnosis of DR and AMD will follow the Early Treatment Diabetic Retinopathy Study [16], AREDS scales [23], and Beckman Initiative Classification [23] (Textbox 1). At 8 weeks after screening, referral completion and diagnostic outcomes will be assessed through review of electronic medical records, hospital visit records, and, when necessary, telephone follow-up.

Textbox 1.Confirmatory diagnosis of diabetic retinopathy (DR) and age-related macular degeneration (AMD).Diabetic retinopathyAccording to the Early Treatment Diabetic Retinopathy Study severity scale [24], primarily diagnosed through fundus photography and indirect ophthalmoscopy to identify typical features such as microaneurysms, retinal hemorrhages, hard exudates, and cotton-wool spots (soft exudates).Fluorescein angiography is generally not used as a primary diagnostic tool; however, it may be used in the evaluation of macular ischemia, edema, or neovascularization to inform treatment strategies. It facilitates the verification of the location and extent of lesions.The severity of DR is categorized into 5 stages: no diabetic retinopathy (no DR, stage 0), mild nonproliferative diabetic retinopathy (NPDR; stage 1), moderate NPDR (stage 2), severe NPDR (stage 3), and proliferative diabetic retinopathy (PDR; stage 4).Age-related macular degeneration:According to the Age-Related Eye Disease Study severity scale [25], fundus photography and indirect ophthalmoscopy are primarily used to identify the location, size, and number of drusen.On the basis of the Beckman Initiative Classification [23], AMD is classified into 4 severity levels based on drusen size and pigmentary abnormalities: no AMD (stage 1), early AMD (stage 2), intermediate AMD (stage 3), and advanced AMD (stage 4).When necessary, fluorescein angiography and optical coherence tomography are used to detect the choroidal neovascularization associated with AMD, the presence of macular edema, and retinal pigment epithelium abnormalities.

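### The stated yearly accrual needs three years of randomisation, but the stated dates leave about 12 to 19 months; the sample sizes, accrual rates and completion date cannot all hold

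*Protocol article*

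**What the plan says.** Three places in the protocol article fix the calendar, and one fixes the follow-up.

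- **Sample Size Estimation.** The required numbers, at two-sided 5% and 90% power, are 2612 for DR (1306 per group) and 1650 for AMD (825 per group). For DR: "Approximately 870 participants are expected to be enrolled annually over an anticipated 3-year study period". For AMD: "Approximately 550 participants are expected to be enrolled per year".
- **Abstract, Results.** The study "began on October 2, 2025, and is expected to be completed in December 2027". On the order of the phases: "After the pilot implementation phase without randomization, participants will be randomized 1:1 into two groups".
- **Study Design.** "The pilot phase began on October 2, 2025, and is expected to last for approximately 6 months to 1 year". The same section adds that progression to the second phase is not guaranteed.
- **Referral After a Positive Test.** "At 8 weeks after screening, referral completion and diagnostic outcomes will be assessed".

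**The concern.** Three times 870 is 2610 and three times 550 is 1650, so the yearly figures are the two targets spread over three years. From first enrolment to December 2027 there are only about 27 months, and the first 6 to 12 of them produce no randomised participants. No section gives a faster accrual rate or a later end date.

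The detection rate is a primary outcome, and it also feeds the cost-effectiveness model. If the date were kept and the rates held, a true effect of the assumed size would be missed about one time in two or three, while the protocol states a one in ten risk. If the numbers were kept, the published completion date would be wrong by well over a year. Until the plan says which of the two ends enrolment, the stopping point could be settled during the trial, which is open-label and has no independent data monitoring committee.

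**Working it through.** **1. Reproduce the stated sample sizes.** Two-proportion formula with unpooled variance: n per group = (1.960 + 1.282)² × [p₁(1−p₁) + p₂(1−p₂)] / (p₁−p₂)², divided by 0.70 for referral completion. The squared term is 10.507.

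- DR, 10% v 15%: 10.507 × (0.0900 + 0.1275) / 0.0025 = 914.1; 914.1 / 0.70 = 1305.9. Stated: 1306.
- AMD, 5% v 10%: 10.507 × (0.0475 + 0.0900) / 0.0025 = 577.9; 577.9 / 0.70 = 825.6. Stated: 825.

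The stated numbers reproduce, so the fault is not in the sample size formula.

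**2. Accrual time needed.** 2612 / 870 = 3.00 years; 1650 / 550 = 3.00 years.

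**3. Accrual time available.** The pilot starts on 2 October 2025, so randomisation starts between 2 April 2026 (6-month pilot) and 2 October 2026 (12-month pilot). Completion is given only as a month, so both ends of December are tried; the day is an assumption. The last participant must be screened 56 days earlier for the 8-week outcome review.

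**4. Numbers and power if the trial stops in December 2027 at the stated rates.** N = yearly rate × days / 365.25. Power = Φ( |p₁−p₂| / √{[p₁(1−p₁) + p₂(1−p₂)] / n} − 1.96 ), with n = N/2. The Statistical Analysis section keeps screen-positives without a confirmed diagnosis in the denominator only. The plan's rates are therefore multiplied by 0.70: 7.0% v 10.5% (DR) and 3.5% v 7.0% (AMD).

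| Pilot | End | 8 weeks deducted | Months | DR: N, power | AMD: N, power |
|---|---|---|---|---|---|
| 12 months | 1 Dec 2027 | yes | 12.1 | 879, 45% | 556, 46% |
| 12 months | 31 Dec 2027 | yes | 13.1 | 950, 48% | 601, 49% |
| 6 months | 1 Dec 2027 | yes | 18.1 | 1315, 61% | 831, 62% |
| 6 months | 31 Dec 2027 | yes | 19.1 | 1386, 64% | 876, 64% |
| 12 months | 31 Dec 2027 | no | 14.9 | 1084, 53% | 685, 54% |
| 6 months | 31 Dec 2027 | no | 21.0 | 1520, 68% | 961, 68% |

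Example, DR, fourth row: n = 693; √[(0.0651 + 0.0940) / 693] = 0.01515; 0.035 / 0.01515 = 2.31; Φ(0.35) = 0.64.

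With the 8-week deduction, N is 34% to 53% of target for both diseases. If power is instead computed as the plan sized the trial (undiluted rates on 70% of N), the same four rows give 47% to 66%, and the last row gives 70%. At the full N, the diluted rates give 89% for both diseases, so the dilution itself costs only about a point.

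**5. Most generous count.** Counting every day from 2 October 2025 to 31 December 2027 (820 days, 2.25 years), pilot included and no follow-up deducted, gives 1953 of 2612 and 1235 of 1650. The targets are still missed.

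**6. What each remedy implies.**
- Keep N and the rates: three years from April or October 2026 ends enrolment in April or October 2029, and the 8-week review ends in late May or late November 2029.
- Keep N and the date (31 December 2027, 8 weeks deducted): DR 2612 / 1.593 = about 1640 a year to 2612 / 1.092 = about 2390 a year; AMD 1650 / 1.593 = about 1040 to 1650 / 1.092 = about 1510. This is about 1.9 to 2.7 times the stated rates.

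**The case against.** A reader might infer that the trial will have only about half its stated power. The protocol does not support that. It sets no calendar stopping rule, calls 2612 and 1650 the required sizes, and gives December 2027 only as an expectation. If the required numbers govern, power stays near 90% and the date slips. The 90% is stated for those numbers and is correct there to within about a point. This objection stands: the power loss is one of two possible consequences and is conditional.

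The yearly figures equal N divided by three, so they may be nominal averages rather than recruitment capacity. The three years may also have been counted from the funding in September 2024. That is plausible, and the document gives no clinic volumes from which to judge whether faster accrual is feasible. It does not remove the conflict, because nobody can be randomised before a pilot that began in October 2025 has ended, and the printed rates are the only ones available.

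A reader might also suspect that pilot participants will be counted toward the targets. The text already rules this out: the abstract describes the pilot as non-randomised, and the Statistical Analysis section bases the primary analysis on randomised participants. No further statement is needed.

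The dates and rates are all hedged, and progression to the second phase is not guaranteed. Hedging covers a drift of some months, not a window of 12 to 19 months in place of 36.

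**Conclusion.** The inconsistency is established from printed figures alone and holds under every reading tried: the targets, the yearly rates and the completion date cannot all be true. The size of the consequence depends on which figure gives way.

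- If the calendar governs and the stated rates hold, about 880 to 1390 DR and 560 to 880 AMD participants are randomised, with power of about 45% to 64%, or up to about 68% if the 8-week review is allowed to run past the end. This rests on the plan's own detection and referral rates, diluted by 70% as its primary analysis requires, and on an assumed day in December.
- If the required numbers govern, power is about 89% to 90% and completion falls in 2029.

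This is an error of timetable, not of sample size calculation, and it should be settled before randomised enrolment is well advanced.

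**What to change.** Reconcile the Abstract (Results), Study Design and Sample Size Estimation. First, state whether enrolment ends when 2612 DR and 1650 AMD participants have been randomised or on a calendar date. Then correct whichever figure follows:

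- **The numbers govern, rates as stated:** move the expected completion to 2029.
- **Both the numbers and the date are kept:** replace 870 and 550 a year with about 1640 to 2390 (DR) and 1040 to 1510 (AMD), according to pilot length, and say what makes those rates attainable.
- **The date governs, rates as stated:** give the expected number randomised by December 2027 and its power in place of 90%.

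In each case, replace the three-year study period with the planned length of randomised enrolment. The change itself is a few sentences and adds no procedure. The real cost is what has to be admitted: a later date, a heavier recruitment commitment, or a lower stated power.

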## Introduction

Diabetic retinopathy (DR) is one of the most common retinal vascular diseases and a microvascular complication of diabetes, affecting approximately one-third of patients with diabetes [1]. It primarily impacts the retinal microvasculature and leads to retinal hemorrhages, microaneurysms, lipid exudates, and, in severe cases, neovascularization [2]. DR is a leading cause of vision impairment and blindness [3]. As the global aging population increases, the number of older individuals with diabetes continues to grow, contributing to a rising prevalence of DR [4,5]. Age-related macular degeneration (AMD), which affects the macula in individuals aged >50 years and is a leading cause of irreversible blindness, has an overall prevalence rate of 8.69% [6]. Early-stage AMD features drusen and abnormalities of the retinal pigment epithelium, while late-stage AMD is classified into 2 forms: neovascular (wet or exudative) and nonneovascular (dry, nonexudative, or atrophic) [2,3].

Effective screening and prompt intervention are crucial for preventing permanent vision loss. However, patients with diabetes and older people often have limited awareness of DR and AMD, poor compliance with fundus checks, and delayed seeking medical help. As chronic disease management mainly takes place in general medicine clinics, where physicians might find interpreting retinal images challenging, timely referrals to ophthalmologists are crucial. Introducing a reliable screening tool in general medicine settings can increase access to fundus examinations, enhance early diagnosis, and improve treatment outcomes.

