### Performance of AI-Assisted Ophthalmic Screening Tools

Both screening tools are based on the convolutional neural networks for image segmentation and classification of disease severities. Both tools received approval from the Taiwan Food and Drug Administration in 2020 (MOHW-MD-No.006966 and MOHW-MD-No.007652), with both classified as “Class II medical devices.” Once installed on a compatible computer, the software will automatically assess image quality and generate preliminary diagnostic outputs, which are immediately shared with attending physicians to support clinical decision-making. VeriSee DR uses deep learning algorithms to identify key DR features, including microaneurysms, hemorrhages, soft exudates, and hard exudates. The tool also offers referral recommendations, categorized as routine follow-up or ophthalmology referral.

The diagnostic accuracies of VeriSee DR and VeriSee AMD have been previously reported [13,26]. For DR, prior validation studies reported a sensitivity of 92.2% and a specificity of 89.5% [13]. For AMD, the results were 90% and 92.4%, respectively [26]. Figure 5 illustrates the AI-assisted screening interfaces for DR and AMD. For DR, the interface displays image quality assessment and AI-assessed severity staging with lesion-level annotations, whereas for AMD, the interface provides an AI-generated referral recommendation.

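### The AMD sample size rests on AI doubling AMD from 5% to 10%, a rate the protocol's own prevalence, sensitivity and referral threshold do not support; on those figures 825 per group gives about 75% power

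*Protocol article*

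**What the plan says.** All of this is in the protocol article.

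- **Sample Size Estimation, background rates:** "The estimated prevalence of any DR (across stages 1-4) and AMD is 27% and 10%, respectively". The stage mix of the 10% for AMD is not given.
- **Sample Size Estimation, AMD:** for patients aged 50 or over in the trial clinics, "the prevalence of AMD is 5%, which is assumed to increase to 10% with the use of AI-assisted diagnostic tools". The section continues: "Assuming that 70% of the screening cases can be successfully referred to ophthalmologists". With two-sided α of 0.05 and β of 0.10 it arrives at 825 per group (1650 in total).
- **Introduction:** AMD "has an overall prevalence rate of 8.69" per cent.
- **Performance of AI-Assisted Ophthalmic Screening Tools**, on sensitivity and specificity: "For AMD, the results were 90% and 92.4%, respectively".
- **Referral After a Positive Test:** "ophthalmology referral will be provided for participants with DR of stages 2 to 4 or AMD of stages 3 to 4". Everyone else is advised to have annual follow-up.
- **Primary Outcome and Statistical Analysis:** the detection rate is confirmed cases over all screened. Screen-positive participants without a confirmatory diagnosis stay in the denominator and do not enter the numerator.

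**The concern.** The planned AMD effect is a change in prevalence. A reading aid changes how many existing cases are found, not how many exist, and under 1:1 randomisation both arms have the same expected prevalence. Taken literally, the effect cannot occur.

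The natural repair is to read 5% and 10% as detection rates, as the DR paragraph does. The 10% then equals the entire AMD prevalence quoted a few lines earlier and exceeds the Introduction's 8.69%. That leaves no room for imperfect sensitivity or for AMD below the referral threshold.

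Detection rate is a primary outcome. If its planned effect cannot be reached on the protocol's own figures, a null AMD result could reflect an optimistic planning assumption rather than the tool.

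**Working it through.** **1. Reproduce the stated size.** Two-proportion normal formula with unpooled variance, two-sided α 0.05, power 0.90, 5% vs 10%, then divided by 0.7:

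n = (1.960 + 1.282)² × (0.05×0.95 + 0.10×0.90) / (0.10 − 0.05)² = 10.507 × 0.1375 / 0.0025 = 577.9

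577.9 / 0.7 = 825.6, against 825 stated. The same method for DR (10% vs 15%) gives 914.1 / 0.7 = 1305.9, against 1306 stated. The arithmetic is sound, so the issue lies in the AMD input rates.

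**2. Put the planned rates on the outcome's scale.** Non-attenders stay in the denominator, so 70% completion scales the rates: 5% × 0.7 = 3.5% and 10% × 0.7 = 7.0%. Power at 825 per group is 89%. Handling the 70% by inflating n instead of scaling the rates therefore costs only about one point and is not the driver.

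**3. What the protocol's figures yield in the AI arm.** Confirmed detection = prevalence of referable AMD × sensitivity × completion.

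| Prevalence | Sensitivity | Before referral loss | After 70% completion |
|---|---|---|---|
| 10% (Sample Size Estimation) | 90% | 9.0% | 6.3% |
| 10% | 100% | 10.0% | 7.0% |
| 5% (literal clinic prevalence) | 90% | 4.5% | 3.15% |
| 5% | 100% | 5.0% | 3.5% |

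At 90% sensitivity, 10% detection before referral loss needs a referable prevalence of 0.10 / 0.90 = 11.1%, above every AMD prevalence in the protocol. At 5% prevalence, 10% is out of reach at any sensitivity.

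**4. Power at 825 per group, control held at the implied 3.5%, AI arm at 6.3%.**

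SE = √[(0.035×0.965 + 0.063×0.937) / 825] = 0.01061

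(0.063 − 0.035) / 0.01061 = 2.64, and Φ(2.64 − 1.96) = 0.75

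A pooled-variance test also gives 75%. For 90% power about 1247 per group (2494 in total) would be needed. In the plan's own framework (5% vs 9%, effective n = 825 × 0.7 = 577.5) power is 76%.

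**5. How far this moves with the assumptions.**

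| Scenario (10% prevalence, 70% completion) | Control | AI | Power at 825 per group |
|---|---|---|---|
| AI sensitivity 90%, as reported | 3.5% | 6.3% | 75% |
| Physician plus AI 95% (assumed) | 3.5% | 6.65% | 83% |
| 100%, all AMD at stages 3–4 | 3.5% | 7.0% | 89% |
| Lower control rate (assumed) | 2.95% | 6.3% | 90% |
| Half of AMD at stages 3–4, sensitivity 50% control and 90% AI (assumed) | 1.75% | 3.15% | 45% |

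The protocol does not give the share of AMD at stages 3 to 4. The last row shows the effect of one assumed share.

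**The case against.** Several points on the other side stand.

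- **The 6.3% is not a hard cap.** The 90% is the software's validation sensitivity. Physicians in the AI arm see the images as well and decide on referral, and the Limitations section says uncertain cases will still be referred. Physician plus AI could exceed AI alone. The only firm ceiling is prevalence.
- **The control rate is held at 3.5%.** A lower control rate restores power, as the table shows, although the plan does not assume one.
- **The effect of the referral threshold is not quantifiable.** The primary outcome counts a confirmatory diagnosis of AMD without limiting it to stages 3 to 4, so an over-graded participant confirmed with early AMD would count.
- **825 per group may understate the AMD analysis.** The Randomization section sets up one cohort in which participants eligible for both conditions can enter both analyses. If the 2612 and 1650 were recruited separately, 2494 would be reached once (2494 − 1650) / 2612 = 32% of DR participants were aged 50 or over and contributed. Neither the overlap nor the age mix is given.

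A reader might also infer stronger claims that the protocol does not support.

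- **That power is at most 75%.** The first two points above show it is not an upper bound.
- **That power falls to 49% at the Introduction's 8.69%.** That figure lowers prevalence while holding control at 3.5%, which raises the implied physician sensitivity from 50% to about 57.5%. With 50% kept, the rates are 3.04% vs 5.47% and power is 69%.
- **That the DR calculation fails in the same way.** The DR text speaks of patients diagnosed and says "Using AI-assisted diagnostic tools, the detection is assumed to increase to 15" per cent, against an any-stage prevalence of 27%. At the reported 92.2% sensitivity, 15% detection implies a stage 2 to 4 prevalence of about 0.15 / 0.922 = 16.3% or more. No figure in the protocol contradicts that.

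**Conclusion.** The point holds for AMD. As worded, the planned effect is impossible. Read as detection rates, 10% in the AI arm uses up the whole stated prevalence and conflicts with the reported 90% sensitivity. The 90% power therefore does not follow from the protocol's own AMD figures, which give about 75% at 825 per group.

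The 75% rests on four assumptions: all of the 10% prevalence is referable, sensitivity in the AI arm equals that of the software, the control arm confirms 3.5%, and 825 per group are analysed. Relaxing the second or third moves power to between 83% and 90% in the scenarios shown; relaxing the first lowers it. More analysed participants would raise it. It is not established that the trial will be underpowered for AMD, only that the stated justification does not support the stated power.

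**What to change.** In Sample Size Estimation, replace the statement that AMD prevalence rises to 10% with confirmed AMD detection rates per screened participant. Derive them in each arm as prevalence of referable AMD × sensitivity × 70% completion, with each input stated and sourced. State whether the 5% is a clinic prevalence or a control-arm detection rate.

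Then restate the power that 825 per group gives: about 75% on the protocol's own figures, with the range above. If participants who also qualify for DR screening are expected to enlarge the AMD analysis, give the expected number and count it explicitly. Check referable prevalence and completion against the pilot before randomisation starts. For DR, a sentence noting the implied stage 2 to 4 prevalence of about 16.3% or more would be enough.

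The cost is a protocol wording change and probably a lower stated AMD power or a larger AMD target. The pilot is already collecting data, and progression to the randomised phase is still to be decided.
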